**Fig. 3 Fig3:**
[figure not shown]
Participant schedule in accordance with SPIRIT 2013 guidelines. The *flow diagram* identifies the time points during the study including Enrolment (admission), Allocation (admission), post-allocation (0, 48 h, discharge), and close-out (end of study). Relevant actions of enrolment, interventions, and assessments performed at the respective time points are marked with an X on the diagram

### Outcome measures

Our study’s primary endpoint is mortality at 48 h after admission. We will also evaluate several secondary outcome measures, including in-hospital mortality (time to death), length of hospital stay, duration of supplemental O_2_ therapy (time to wean O_2_), O_2_ delivery system failure(s), cost (installation, servicing, and maintenance), baseline and retained nursing skills in managing oxygen therapy, etiology (based on polymerase chain reaction of dried blood sample and nasopharyngeal swabs), as well as diagnostic and prognostic host biomarkers (Additional file 4).

### Data monitoring

Data will be routinely monitored on each site by a dedicated data collection officer or study nurse, who will be responsible for recording patient information, follow-up, and uploading data to trial databases through KoBoCollect on tablet PCs. During entry, any missing data will be noted on an Errors/Omission log which will be checked regularly by the study team to fill in the missing data. Once uploaded, study data will be securely stored in a locked room and on a password-protected device, accessible only to study personnel. The study monitor or other authorized representatives may inspect all documents and records required to be maintained by the principal investigator; the study site will permit access to such records.

Adverse events (AEs) and unintended effects of SPO_2_ will be monitored, reported, and collected by clinical staff, and will be managed according to national and local standard of care. AEs will be monitored continuously during the study by a dedicated nursing staff. A running log of AEs will be kept and reviewed periodically to allow the study team to assess if any patterns of AEs emerge in real time. All study deaths will require completion of a serious AE form, which will be made available to ethics boards and regulatory authorities within seven days of the event.

No interim data analysis or trial stopping rules are planned for this trial. Oxygen is known to be an essential and life-saving therapy and the efficacy of the SPO_2_ system has been shown to be non-inferior compared to conventional oxygen therapy in the Ugandan context [15]. The stepped-wedge design and commitment to participating sites demands that SPO2 be installed at all sites, such that trial discontinuation at midpoint is not feasible. Because we do not plan to halt the trial before enrolling the planned number of clusters, we have not planned for a Data Monitoring Committee (DMC).

### Statistical considerations

In our trial, we have a cluster-randomized design. The primary dependent variable is the 48-h mortality. The independent (predictor) variable of interest is the exposed/unexposed status of an individual patient (fixed effect), which will depend on whether the patient presents to a participating site before or after installation of SPO_2_. Furthermore, we have covariates which will be modeled as both fixed and random effects. We will use a LME logistic regression model to examine the effect of SPO_2_ on mortality while adjusting for changes in mortality over time (fixed effect) and variability in mortality between sites (random effect). We will use *R* [19] and *lme4* [20] to model the binary outcome (survival) as a function of SPO_2_ treatment, calendar time, and site. As fixed effects, we will enter SPO_2_ treatment (before or after SPO_2_ installation) and calendar time, without interaction term, into the model. We will model site as a random effect. We will determine the statistical significance of the SPO_2_ treatment effect comparing models with and without the SPO_2_ treatment term. If the model fit is significantly improved with inclusion of the treatment term, at α = 0.05 level of significance, we will conclude that the SPO_2_ treatment effect is statistically significant. We will estimate the 95% confidence interval of the treatment effect (odds ratio) from the coefficient of the LME logistic regression model.

Secondary outcomes will be assessed using descriptive and comparative statistics, as appropriate. Where possible, LME models accounting for the clustered data structure and effects of calendar time will be used to determine differences between SPO_2_-treated and untreated patients, with necessary adjustments being made to allow for multiple comparisons within secondary outcomes.

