### Study design

The study will be a stepped-wedge cluster RCT. This trial will not be blinded. Clusters (health facilities) will be randomly allocated to the timing of implementation of the SPO_2_ system. The installation of SPO_2_ will not be simultaneous but will proceed in accordance with the stepped-wedge design (Fig. 1). All health facilities will have a run-in period during which nurses will be trained in pulse oximetry, O_2_ management, and the study protocol. Data collection (prospective enrolment and accurate electronic record-keeping) will be in place by the end of the run-in period. SPO_2_ will be introduced one site at a time, on a monthly basis, until all 20 sites have SPO_2_ installed. The timing of installation of SPO_2_ will be random, with allocation concealment. Analysis will compare mortality before and after implementation of SPO_2_, using linear mixed effects (LME) logistic regression, adjusting for the confounding effects of time (fixed effect) and site (random effect) [17]. Data collection will continue until the trial’s termination, considered to be one month after the installation of SPO_2_ in the 20th site.

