### Participants

We will include patients presenting to the selected sites meeting the following inclusion criteria: (1) age < 5 years; (2) hypoxemia (SPO_2_ < 92%) based on non-invasive pulse oximetry taken within 24 h of admission, on room air; and (3) warrant hospital admission based on clinical judgement. Patients will be excluded from the study if: (1) measured SPO_2_ ≥ 92%; (2) they can be managed as an outpatient; (3) parents or guardians unwilling to provide written informed consent to participate in study; (4) known cyanotic cardiac condition; and (5) diagnosis of hypoxic ischemic encephalopathy in a neonate.

Screening procedures will be as follows: children aged < 5 years presenting to the participating facilities will be screened for hypoxemia using a portable pulse oximeter if they have cough and/or difficulty breathing. Past medical history will be reviewed with the parent or guardian for known cyanotic cardiac condition and/or hypoxic ischemic encephalopathy. If the patient meets eligibility criteria, the parent or guardian will be approached for informed consent.

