### Study procedures

For eligible participants, the parent or legal guardian will be approached for consent to participate in the study (Additional file 3). If granted, the patient will be admitted to the pediatric ward, where there will be a SPO_2_ system installed or not, according to random timing of installation at each site. All patients will receive standard care for their underlying disease, including antibiotics for pneumonia, intravenous fluids as necessary, blood transfusion as necessary, antipyretics, and any other medical therapy required. The study will ensure there are no stock-outs of essential medications or equipment. Basic demographic and clinical data will be collected from the case admission record, and patients will be followed during their hospital admission. The primary outcome, death at 48 h after admission, will be recorded. Other outcomes could include death after 48 h, discharge, and transfer to another facility. Death at 48 h (versus other) will later be analyzed as a binary variable. Patients discharged or transferred to another facility will be followed up by telephone at 48 h after admission to assess status.

During hospitalization, secondary outcomes will be recorded, including vital signs at admission and daily thereafter until discharge. Oxygen saturations will be monitored on a 4-hourly basis, during oxygen administration and after. Oxygen utilization (flow rate, duration) will be recorded throughout hospitalization. The need for oxygen therapy will be assessed daily, using standardized criteria for weaning oxygen. The length of stay among survivors will be recorded, as well as the final patient disposition (discharged without disability, discharged with disability, transferred to another facility, or death). The participant flow is illustrated in Fig. 3.

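### The primary model has no patient-level covariate, so a case-mix shift that coincides with a site's own installation would be read as an SPO2 effect

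*Protocol article*

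**What the plan says.** **Blinding and exposure.** Study design states: "This trial will not be blinded". Under Statistical considerations a child's exposure is a status "which will depend on whether the patient presents to a participating site before or after installation of SPO_2". Study procedures describes what follows consent: "If granted, the patient will be admitted to the pediatric ward, where there will be a SPO_2_ system installed or not". Whoever admits and seeks consent can therefore see the site's status.

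**Entry.** Participants requires room-air saturation below 92%, "based on non-invasive pulse oximetry taken within" 24 h of admission. Two further gates are discretionary: the child must "warrant hospital admission based on clinical judgement", and children are excluded if they have "parents or guardians unwilling to provide written informed consent to participate in study".

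**Model.** Statistical considerations fixes the primary analysis as a mixed logistic model that will "model the binary outcome (survival) as a function of SPO_2_ treatment, calendar time, and site". Treatment and calendar time are the fixed effects and site is the random effect. The abstract, Study design and Sample size give the same model. The covariates mentioned in that section are only time and site.

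**Other relevant text.** The only sensitivity analysis described (Discussion) concerns cluster dropout. The Discussion rests scientific validity on adjustment for site and time, and its limitations do not mention patient selection. The power simulation (Sample size) gives each child the mortality of the site, reduced by treatment, with no variation in severity between children.

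**The concern.** Randomising the order of installation balances sites over time. It does not balance children recruited after a site's status is known. Site selection reports oxygen available for pediatric use at only 3 of 20 sites, so installation is a large and visible change. It could plausibly alter who is kept, referred elsewhere or consented.

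The site effect absorbs stable differences between facilities, and the time effect absorbs drift that all facilities share. A change in case mix that begins at each site in its own installation month has the same pattern as the treatment indicator, so its effect on mortality goes into the SPO2 coefficient. Less ill children after installation would imitate a benefit. Sicker children, for example because they are no longer sent elsewhere, would hide one.

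**Working it through.** **Inputs from the protocol.** 20 sites, one crossing over per month, 2400 patients, baseline mortality 15%, 35% reduction, α = 0.05, mixed logistic model with time fixed and site random. The design effect is 15% to 9.75%, so OR = (0.0975/0.9025)/(0.15/0.85) = 0.108/0.176 = 0.61.

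**Assumed, because the documents do not give them.** Between-site SD of log-odds, variation in site volume, linear time, and every case-mix shift below.

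**1. The plan's own power.** The protocol states 80% for 2400 patients and 82% for a median of 2600 with four-week steps. A simulated stepped wedge (random-intercept logistic model, likelihood-ratio test, between-site SD 0.2, volume CV 0.6, 21 periods) gives 78% at 2400 and 81% at 2600. At 2400, over SD 0 to 0.8 and the other settings tried, power runs from 64% to 89%. The stated figure is plausible but cannot be verified without the site data.

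**2. Shift linked to installation, true effect zero.** Let extra enrolment after installation be a fraction e, at relative mortality r. Post-installation mortality is then p × (1 + e·r)/(1 + e), with p = 0.15 and r = 0.25. The simulation uses between-site SD 0.5.

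| e | Mortality after | OR by formula | OR simulated | Rejects |
|---|---|---|---|---|
| 0 | 15.0% | 1.00 | 1.02 | 6% |
| 0.1 | 14.0% | 0.92 | 0.93 | 8% |
| 0.2 | 13.1% | 0.86 | 0.85 | 17% |
| 0.3 | 12.4% | 0.80 | 0.80 | 28% |
| 0.5 | 11.3% | 0.72 | 0.70 | 48% |

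For e = 0.3: 0.15 × 1.075/1.3 = 0.124, and OR = (0.124/0.876)/0.176 = 0.80.

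**3. Drift common to all sites.** When the extra lower-risk enrolment rises with calendar time at every site alike, the planned model gives OR 0.99 to 1.01 and rejects in 5% to 8%. The time term does its job.

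**4. What adjustment recovers.** Here 30% of baseline enrolment is already lower-risk (a quarter of the mortality of the others), the true effect is zero, and there are 500 runs per cell.

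| Extra lower-risk | Planned model | Severity measured perfectly | Severity 75% correctly classified |
|---|---|---|---|
| 30% | OR 0.83, rejects 19% | OR 1.00, 6.6% | OR 0.86, 13% |
| 50% | OR 0.74, rejects 39% | OR 1.00, 5.6% | OR 0.79, 26% |

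The Monte Carlo standard error at 19% is √(0.19 × 0.81/500) = 1.8 points. With 75% correct classification, the share of the bias removed on the log scale is 1 − ln 0.86/ln 0.83 = 1 − 0.151/0.186, about a fifth.

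A continuous version gives the same message. With a 0.3 SD shift, severity OR 2.2 per SD and between-site SD 0.4, the crude expectation is 0.3 × ln 2.2 = 0.24 on the log scale. The simulated unadjusted log OR is −0.23. Adjusted, it is −0.01 if severity is fully captured, −0.13 if half is captured and −0.18 if a quarter is.

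**5. Opposite direction, and no shift.** These runs use 300 trials of 2400 patients, severity OR 1.65 to 2.2 per SD, and severity measured perfectly. With the true effect present and post-installation enrolees 0.2 SD sicker, power is 38–44% unadjusted and 65–67% adjusted. With no shift, adjustment gains 2 to 4 points of power.

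**The case against.** **Entry is largely objective.** The saturation threshold is measured, symptomatic children under 5 are screened by oximeter in both periods, and staff are trained in oximetry and the protocol during the run-in, before the first step. Detection should not therefore begin with installation. This stands, and it narrows the room for selection. It does not close it, because severity still varies below 92% and admission by judgement and consent remain.

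**No shift is shown.** This also stands. A reader might infer that the result will be biased, or that any change in case mix biases it; the documents support neither. Small shifts matter little: 0.1 to 0.15 SD gave 4–9% rejection, against about 7% with none.

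**Adjustment may not cure it.** A reader might infer that age and saturation would remove most of a shift. That holds only if they capture severity almost completely, and saturation is already truncated by eligibility.

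**An unadjusted primary model is conventional, and the unseen SAP may add an adjusted one.** This stands in part. The protocol does not leave the model terms open, and an adjusted analysis carries more weight if it is prespecified.

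**Time zero.** The timing of the qualifying reading, set beside "If granted, the patient will be admitted to the pediatric ward", may suggest an inconsistent start and tempt a reader to run the 48 h from the first reading. The documents do not support that. Study procedures and Outcome measures both count from admission, and the admission phrase can describe placement on the ward. Moving the clock would change the primary endpoint of a recruiting open-label trial. It would also add immortal time, because a child who dies between the reading and consent is never enrolled.

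**Conclusion.** The point holds as a conditional weakness. Enrolment is open label and partly discretionary once status is known, and the fixed primary model contains nothing that could separate an installation-linked change in case mix from an SPO2 effect.

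The size depends wholly on the assumed shift. In the first set of runs, with true effect zero, it ranges from negligible (10% extra lower-risk enrolment: OR 0.93, 8% rejection) to serious (50% extra: OR 0.70, 48%, against a design OR of 0.61). The direction could equally be the reverse, with loss of power. Covariate adjustment is a partial protection, somewhere between about a fifth and all of the bias in the settings examined. That is why enrolment around installation also has to be shown. The improvement is worth making because it costs almost nothing, not because bias has been demonstrated.

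**What to change.** 1. In the mixed logistic model for 48-h mortality, prespecify age and admission room-air saturation as continuous fixed effects, alongside treatment, calendar time and the random site effect. State which reading is used if a child has more than one.
2. Report the model with treatment, time and site only alongside it.
3. Tabulate the number enrolled, age and admission saturation by month relative to each site's installation, so that a reader can judge whether case mix moved.
4. Keep the endpoint at 48 h after admission.

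**Cost.** Wording in the analysis plan and one table. Age and saturation both determine eligibility, so no new data item is needed. The odds ratio becomes conditional on the two covariates, which should be said when it is reported. Because recruitment has begun in an open-label trial, the change should be dated and fixed before any comparison of mortality by installation status. The protocol plans no interim analysis, so this is feasible.

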### Sample size

We will include 20 health facilities and a total of 2400 hospitalized patients. This sample size was calculated using a computer simulation, modeling trial conditions and applying the planned statistical analysis. Although analytic methods for sample size calculation for cluster-randomized stepped-wedge trials have been published [21], these require estimates of nuisance parameters (e.g. intra-cluster correlation coefficient) which were not available in the Ugandan context, such that the validity of this method was unknown.

For simulation parameters, we used data from the Demographic and Health Information System (DHIS) 2015 for Uganda. This database contains information on the number of patients with clinical pneumonia admitted to each hospital and the number of fatal cases, allowing us to estimate site-specific pneumonia mortality. In a computer simulation, we randomly selected 20 representative sites from the DHIS and used the number of patients admitted with pneumonia at each site to estimate the incidence of hypoxemic patients (13% [22]) that would be enrolled in a hypothetical clinical trial. The monthly number of hypoxemic pneumonia admissions was modeled as a Poisson distribution [23]. Monthly random allocation of SPO_2_ to the 20 sites was simulated, according to the stepped-wedge design. The outcome of each patient at 48 h was modeled as a Bernoulli trial with probability of fatal outcome equal to the site-specific mortality. We used DHIS 2015 data to estimate the baseline mortality assuming a mortality reduction of 35% after installation of SPO_2_ [13]. Having generated simulated trial data, we ran the planned statistical analysis, fitting a LME logistic regression model, as described above. Mortality was modeled as a function of SPO_2_ treatment, with adjustment for covariates of calendar time (fixed effect) and site (random effect), and the *p* value for the treatment effect was calculated. We repeated the simulation > 5000 times and determined the proportion of trials that correctly detected a difference between patients receiving SPO_2_ and those not receiving SPO_2_ (statistical power). Using this simulation strategy, 20 sites enrolling a total of 2400 patients would provide > 80% power to detect a 35% mortality benefit of SPO_2_ at the α = 0.05 level of significance [17, 24]. Data collection could feasibly be completed within 24 months (Fig. 4).

**Fig. 4 Fig4:**
[figure not shown]
*Computer simulation* for sample size estimation. **a** In the simulation, study power varied with the number of clusters and the duration of enrolment, as expected. Approximately 20 sites enrolling patients over 24 months would provide power of 80%. Each dot represents at least 100 simulated trials. **b** Each dot represents one simulated trial with 20 sites and 20 steps, enrolling patients for two weeks (*black dots*), four weeks (*red dots*), or six weeks (*blue dots*) at each step. The study power is approximated by the proportion of trials appropriately detecting a statistically significant effect of SPO_2_ (*p* < 0.05, *dotted line*). The simulation was repeated 3000 times to generate a plot of *p* value and number of trial participants. For trial simulations with four-week steps (total duration 21 months), the median number of participants enrolled was 2600 (interquartile range 2400–2900) and the statistical power was 82%. **c** In the simulation, study power was also sensitive to variations in the assumptions of baseline mortality and mortality reduction. Our base case (15% baseline mortality, mortality reduction of 35%) was associated with statistical power of 80%. Each dot represents at least 100 simulated trials

Figure 4a shows the statistical power as a function of the number of sites and the duration of enrolment. Each power estimate was based on at least 100 hypothetical trials in a computer simulation. Approximately 20 sites were required, enrolling patients for two years, to achieve sufficient statistical power. Figure 4b shows individual trial simulations, illustrating increasing power with increasing sample size. Figure 4c shows the sensitivity of the study power to input parameters: baseline mortality and mortality reduction with SPO_2_.

## Discussion

The global burden of pneumonia mortality is concentrated in resource-constrained settings in Africa and Asia [2, 25–27]. Access to O_2_ remains limited and the need for O_2_ has come to the forefront of global health priorities with the WHO recently adding O_2_ to its Model List of Essential Medicines [28]. Several countries, such as Nigeria and Ethiopia, have begun to develop national frameworks for O_2_ scale-up [29, 30]. With increasing recognition of the importance of O_2_ therapy in low-resource settings, novel methods of O_2_ delivery are required. SPO_2_ offers a reliable and sustainable source of O_2_ that could have utility in these low-resource settings. We hypothesize that we will observe a reduction in mortality in children hospitalized with hypoxemia, after installation of SPO_2_, relative to current level of care. We will test this hypothesis in a stepped-wedge cluster-randomized study in Uganda.

SPO_2_ has a number of benefits that lend themselves to further scale-up: reliability in settings with poor access to electricity or O_2_ cylinders [31]; abundance of solar radiation in target LMICs in the tropics [32]; minimal maintenance and training requirements [32]; and cost-effectiveness after a one-time capital investment for installation of equipment. Our group has already demonstrated the feasibility and effectiveness of SPO_2_ at two resource-limited hospitals [14, 15]. The proposed study will demonstrate mortality benefit of SPO_2_ in a country-wide roll-out, providing key data for decision-makers within public health systems with respect to utility (lives saved) and costs of this technology. To our knowledge, only one previous study has quantified the effect size of improved O_2_ delivery on child mortality in a low-resource context [13]. Additional findings from this trial will be of broad interest, including: pneumonia-related mortality at various thresholds of hypoxemia [11]; oxygen utilization at representative health facilities; engineering aspects and costs (installation and maintenance) of SPO_2_ implemented across an entire country; and training strategies in oxygen delivery for frontline nurses.

The choice of study design is motivated by ethical and pragmatic considerations [24, 33]. The cluster-randomized trial design is modern, innovative, and particularly suited to investigations of community level public health interventions that have been proven effective in individual level trials (i.e. “phase IV” effectiveness trials) [17, 24]. Staged roll-out of O_2_ delivery avoids the ethical concern of randomizing individuals to a “no O_2_” arm. All facilities will transition from control to intervention groups [24, 34], providing permanent access to previously unavailable O_2_ therapy by the end of the trial. The staged approach will ease logistical constraints otherwise associated with implementing interventions all together at the same time [24]. With respect to scientific validity, our statistical plan (LME logistic regression model) will adjust for variability in mortality between different sites (random effect) and temporal trends in mortality (fixed effect). Some risks associated with this design were highlighted in a recent systematic review of 46 individual stepped-wedge studies: clusters dropped after randomization or after data collection had started (six studies); delay in implementation of interventions (four studies); and clusters not receiving the intervention at all (five studies) [33]. To mitigate this risk, we have selected two back-up sites that may be recruited in case of cluster dropout. Although this mitigating strategy compromises the stepped-wedge design, it may be necessary to achieve the desired sample size. In case of cluster dropout and addition of new clusters, the statistical plan will include sensitivity analyses including sites planned *a priori* and a pragmatic analysis of all sites ultimately included.

Our study sample size was calculated via a computer simulation using real-world parameters using the Uganda DHIS [22, 35], data from previous large-scale studies [31], and systematic reviews [22]. We applied our planned primary analysis to the simulated data for > 5000 trials to estimate a required sample size of 2400 patients from 20 sites, with 20 steps, recruited over two years to detect a mortality benefit estimated at 35% with 80% power (α = 0.05). Other published stepped-wedge trials in a recent systematic review were of comparable size: median number of participants of 1720 (range 16–292,000), 2–190 clusters, 2–15 steps, over a median period of 20 months (range 9 days to 4 years). Our approach, using computer simulation, has been recommended by previous authors, who noted advantages of simulation-based methods to overcome some of the limitations of analytical formulae and in dealing with the specific features of the study [36].

In addition to our scientific objectives, this study aims to build capacity among frontline nurses for monitoring and delivery of supplemental O_2_ therapy, including pulse oximetry. A study conducted to assess pulse oximetry knowledge and training needs in ward nurses and doctors concluded that only 16% of participants had received any formal training for pulse oximetry and 65% of the participants expressed the need for more training [37]. In another report from Uganda, most nurses were comfortable with the use of oxygen concentrators but were not familiar with pulse oximetry [6]. To address this gap, recognizing context-specific challenges of implementing pulse oximetry [38], SPO_2_ study will train nursing staff in pulse oximetry and safe delivery of O_2_. With enhanced knowledge, skills, and availability of equipment (pulse oximeters and SPO_2_ equipment), our study will improve the quality of care provided to hypoxemic patients during the study and after the study has ended.

Our study has several limitations. The multi-center stepped-wedge design involving health facilities within the public sector, is vulnerable to some external challenges that may not be directly influenced by the researchers (e.g. change of hospital staff or withdrawal of clusters from the study) [33, 39]. The health facilities participating in this study will be in rural or remote communities in Uganda, such that generalizability of our findings to urban or resource-intensive facilities will be limited. The etiology of hypoxemic illness will not be precisely identified. Radiographic confirmation of pneumonia and microbiological confirmation of the infectious etiology would be desirable, but the requisite radiology and lab services are not available in most centers where SPO_2_ will be installed. Additional laboratory testing such as blood culture, sputum culture, viral studies, and a panel of infectious diseases serology would be necessary to definitively diagnose conditions such as pneumococcal pneumonia and viral respiratory tract infections. However, resource limitations preclude an exhaustive battery of diagnostic tests in our setting. Although precise microbiological etiology may not be known, mortality (primary outcome) as well as length of stay (secondary outcome) are clinically meaningful outcomes that can be assessed unambiguously in the context of our study. This study will allow us to demonstrate the mortality benefit of SPO_2_ for treatment of hypoxic respiratory illness, irrespective of etiology, and is similar to the diagnostic capacity of other health facilities where SPO_2_ would potentially be implemented.

Given the magnitude of pediatric pneumonia deaths, estimated at 900,000 per year [40], a life-saving, cost-effective intervention such as SPO_2_ could represent an important tool for the improvement of global child survival. Demonstrating a mortality benefit of SPO_2_ will provide strong supportive evidence for the system and could catalyze the widespread implementation of SPO_2_ in resource-limited settings across Africa and Asia.

